#### Efficiency

Outcomes will be expressed as incremental cost-effectiveness ratios (ICERs) (i.e., the difference in overall mean direct medical costs divided by the difference in mean QALYs between the two groups) and cost-effectiveness acceptability curves. The absence of intervention will be considered as the reference strategy. Costs and QALYs will be discounted at a rate of 3 % per annum. The robustness of results will be assessed through a one-way sensitivity analysis based on the use of the SF-6D. A standard nonparametric bootstrap simulation will also be conducted (10,000 replications) to estimate the 95 % confidence interval of the ICER.

In case of missing assessments concerning utility scores, the last observation will be carried forward. Differences in mean utility scores and mean costs between the intervention and control groups will be assessed by the nonpaired *t* test (for variables with a normal distribution) and the nonparametric Mann-Whitney test (for variables with a nonnormal distribution).

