The purpose, in terms of public health, is to avoid the health deterioration of caregivers, and thus indirectly, to improve the patient’s health status through optimized management that is potentially inexpensive and economically acceptable for society. The intervention study is based on the hypothesis that early intervention during the initial phase of the care relationship is likely to improve the caregivers’ HRQoL and the quality of the support provided. The hypothesis of the associated efficacy study is that the intervention of a social worker, through their role in listening, alerting, advising and guiding, may improve the wellbeing of informal caregivers, and thus reduce their potential consumption of health care resources, and consequently, the expenditure related to their care mission. Improving caregivers’ HRQoL and preventing degradation of their health will make it possible to positively influence the patients’ HRQoL, and as a result, their health, autonomy and capacity to continue living at home. To ensure the homogeneity of the intervention across the Burgundy-Franche-Comté region, all registered social workers in the region will undergo study-specific training. The intervention to be provided in the context of this study by social workers is explained in detail and formalized in a partnership agreement signed by all the social services employing social workers in the region.

The ICE cohort may lead to the formulation of health recommendations and serve as a basis for the development of services that offer support to caregivers to reduce the potential risk of social inequalities related to caregiving.

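### The planned bootstrap 95% interval of the ICER cannot be interpreted if replicates are cost-saving with a QALY gain or if the QALY difference straddles zero; an incremental net benefit interval from the same replicates can

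*Protocol article*

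**What the plan says.** The Efficiency part of the Analysis section in the protocol article defines the ICER as "the difference in overall mean direct medical costs divided by the difference in mean QALYs between the two groups". On the comparator it says: "The absence of intervention will be considered as the reference strategy". Results are to be expressed as ICERs "and cost-effectiveness acceptability curves". For precision it adds: "A standard nonparametric bootstrap simulation will also be conducted (10,000 replications"), in order to estimate the 95% "confidence interval of the ICER". It gives no rule for negative replicates or for replicates in different quadrants of the cost-effectiveness plane, and it plans no net-benefit interval.

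The Discussion gives the expected direction. By improving caregivers' wellbeing, the intervention may "reduce their potential consumption of health care resources, and consequently, the expenditure related to their care mission". The same section describes the management as "potentially inexpensive and economically acceptable for society". The ICER is one of the named secondary objectives in the Interventional study section.

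**The concern.** A confidence interval is useful only if moving along its scale means moving from worse to better. The ICER has that property when the intervention costs more and gains QALYs. It loses it in two situations.

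- **Saving with a gain (dominant).** The ratio is negative, and a larger QALY gain at the same saving moves it towards zero, so a better result can look worse. A dominated result (costlier with a loss) is also negative and can give the same number.
- **QALY difference near zero.** The denominator changes sign between replicates, so the ratio jumps between large positive and large negative values. A positive ratio may then mean costlier with a gain or cheaper with a loss.

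The hypothesis in the Discussion, set against a numerator of direct medical costs, points to the first situation. A weak effect on utility would produce the second. In either case the interval may be read as great uncertainty, or as a precise saving, when the replicates say something else.

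**Working it through.** **No figure to reproduce.** The article gives no expected cost difference, QALY difference or SD for the cost-utility analysis. The ordering argument needs none. The illustration uses assumed values.

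**Step 1: ordering, without assumptions about variability.** ICER = dC/dE. Incremental net monetary benefit: INMB = λ × dE − dC, shown at an assumed threshold λ = 20,000.

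| dE (QALY) | dC (cost) | ICER | INMB |
|---|---|---|---|
| +0.02 | -400 | -20,000 | 400 + 400 = 800 |
| +0.04 | -400 | -10,000 | 800 + 400 = 1,200 |
| +0.04 | -800 | -20,000 | 800 + 800 = 1,600 |
| -0.04 | +400 | -10,000 | -800 - 400 = -1,200 |

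Rows 1 and 3 share a ratio, although row 3 is twice as good. Rows 2 and 4 share a ratio, although one is dominant and the other dominated. INMB separates them all.

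**Step 2: inputs for the illustration.**
- Sample size calculation section: 1684 randomized in a large disease group, so 842 per arm; 7224 in total before the allowance for loss to follow-up, so 3,612 per arm.
- Assumed: cost SD 5000; independent, normally distributed mean differences standing in for the bootstrap distribution.
- Scenario 1 (assumed): gain 0.02, QALY SD 0.2, cost difference -300.
- Scenario 2 (assumed): gain 0.01, QALY SD 0.4, cost difference -300.
- SE of a difference = SD × √(2/n per arm).

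**Step 3: scenario 1 at 842 per arm (one large disease group).** SE(dE) = 0.2 × √(2/842) = 0.00975; SE(dC) = 5000 × √(2/842) = 243.7.
- P(dC > 0) = Φ(-300/243.7) = Φ(-1.23) = 0.109.
- P(dE < 0) = Φ(-0.02/0.00975) = Φ(-2.05) = 0.020.
- Dominant: 0.891 × 0.980 = 87%. Costlier with gain: 0.109 × 0.980 = 11%. Cheaper with loss: 0.891 × 0.020 = 2%.
- The 2.5 and 97.5 percentiles of the simulated ratio are about -103,000 and +20,000.
- INMB at 20,000: mean 400 + 300 = 700; SE = √((20,000 × 0.00975)² + 243.7²) = 312; interval 700 ± 1.96 × 312, about 90 to 1,310. This is favourable at that threshold, which the ICER interval does not show.

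**Step 4: scenario 1 at 3,612 per arm (whole trial).** SE(dE) = 0.00471; SE(dC) = 117.7.
- P(dC > 0) = Φ(-2.55) = 0.005; P(dE < 0) = Φ(-4.25), practically zero. So 99.5% of replicates are dominant.
- ICER interval about -34,700 to -3,400. Quadrants are hardly mixed, but the limits still have no better and worse end.
- With a cost difference of +300 instead, the interval is about 3,400 to 34,700 and can be read in the ordinary way.

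**Step 5: scenario 2 at 3,612 per arm.** SE(dE) = 0.4 × √(2/3612) = 0.00941.
- P(dE < 0) = Φ(-0.01/0.00941) = Φ(-1.06) = 0.14, so about 14% of replicates show a QALY loss.
- ICER interval about -308,000 to +269,000. These limits vary by a few thousand between runs because the ratio has heavy tails.
- INMB at 20,000: mean 200 + 300 = 500; SE = √((20,000 × 0.00941)² + 117.7²) = 222; interval about 65 to 935, which remains ordered and readable.

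**The case against.** Five points can be made for the plan.

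- **The acceptability curves already carry the uncertainty.** This stands. Such a curve is the probability that net benefit is positive at each threshold, so it has no ordering problem. Mean costs and mean utilities are also to be compared separately, which shows the sign of each. A reader might infer that the whole uncertainty analysis of the cost-utility result fails; the article does not support that. But the curves do not repair the interval, which is to be estimated as well.
- **A net saving is not asserted.** This stands in part. The Discussion says that the intervention may lower expenditure, and its other wording suggests low cost rather than a saving. A reader might infer that the plan assumes a cost-saving intervention, but no net saving after the cost of the intervention is stated. Still, the numerator is defined on direct medical costs, and those are what the hypothesis expects to fall.
- **The interval can be valid.** This stands. If nearly all replicates are costlier with a gain, it reads normally, as the +300 case shows. So the documents do not support saying that it is meaningless whatever the data.
- **842 per arm is the wrong sample.** This largely stands. The article describes the cost-utility analysis as one comparison of the two arms and states no ICER by disease group, so 3,612 per arm is the more natural scale. There, scenario 1 no longer mixes quadrants, although its values remain unordered, and scenario 2 still fails.
- **The type of interval is left to the analysis plan.** The article indeed does not say percentile. But the fault lies in the ratio scale: limits quoted as ratios do not show which quadrant they come from, however they are obtained. The choice of the ICER as the quantity given an interval is fixed in the article.

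**Conclusion.** The point holds in a limited, conditional form. The planned 95% interval of the ICER fails as a measure of precision if replicates are cost-saving with a QALY gain, the direction hypothesized for health care expenditure, or if the QALY difference straddles zero. It is sound if nearly all replicates are costlier with a gain. The acceptability curves, the ICER point estimate and the primary endpoint are untouched.

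The ordering failure is mathematical and rests on no assumption. The interval widths in the illustration rest entirely on assumed SDs, differences, independence and normality, because the article gives no such inputs. A larger sample reduces the mixing of quadrants in scenario 1 but does not restore the order of negative ratios. The matter concerns one summary of a secondary economic objective, so it is a worthwhile improvement and not a threat to the trial.

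**What to change.** In the Efficiency part of the Analysis section, and in the statistical analysis plan that the article says will be written before database lock:

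- replace the 95% confidence interval of the ICER with a bootstrap 95% interval of the incremental net monetary benefit, λ × dE − dC, over a stated range of thresholds λ;
- report the scatter of replicates on the cost-effectiveness plane, with the percentage in each quadrant;
- keep the ICER as a point estimate, reported as dominant or dominated where it is negative;
- keep the planned acceptability curves.

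The same 10,000 replicates serve all of these. The cost is a change of wording and the choice of a threshold range in advance. No extra data, participants or simulation are needed.

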## Discussion

The scientific purpose of the ICE cohort study is to define longitudinal profiles of caregivers and to evaluate pragmatic action to support them. This study should make it possible to improve our knowledge concerning the life course of caregivers (by identifying profiles of the caregivers and understanding the mechanisms involved in changing this profile), to identify their needs and their expectations (in terms of professional support, financial assistance, information and advice to assist in caregiving) and to envisage optimized support for patients with chronic disease who live at home.

The consideration of patients’ social environment is essential in an integrative approach to the management of their disease. In this respect, the difficulties encountered by caregivers may have direct implications on the quality of the care they provide. This study will allow us to identify factors associated with modifications in patient management support. Improved knowledge of the difficulties that caregivers face in their everyday lives could contribute to identifying potentially high-risk situations in the care relationship (e.g., mistreatment) and make it possible to implement timely support for caregivers at risk of psychological, physical or social distress.

The purpose, in terms of public health, is to avoid the health deterioration of caregivers, and thus indirectly, to improve the patient’s health status through optimized management that is potentially inexpensive and economically acceptable for society. The intervention study is based on the hypothesis that early intervention during the initial phase of the care relationship is likely to improve the caregivers’ HRQoL and the quality of the support provided. The hypothesis of the associated efficacy study is that the intervention of a social worker, through their role in listening, alerting, advising and guiding, may improve the wellbeing of informal caregivers, and thus reduce their potential consumption of health care resources, and consequently, the expenditure related to their care mission. Improving caregivers’ HRQoL and preventing degradation of their health will make it possible to positively influence the patients’ HRQoL, and as a result, their health, autonomy and capacity to continue living at home. To ensure the homogeneity of the intervention across the Burgundy-Franche-Comté region, all registered social workers in the region will undergo study-specific training. The intervention to be provided in the context of this study by social workers is explained in detail and formalized in a partnership agreement signed by all the social services employing social workers in the region.

The ICE cohort may lead to the formulation of health recommendations and serve as a basis for the development of services that offer support to caregivers to reduce the potential risk of social inequalities related to caregiving.

## Trial status

At the time of manuscript submission, a feasibility study conducted to test the inclusion mechanisms in the clinical departments, as well as the questionnaire concerning the designation of the principal caregiver, has been completed. The feasibility study that was carried out from 2013 to 2015 allowed us to test the acceptability of the study and the questionnaires with the patients and their caregivers, to better understand the logistic and operational aspects. The project protocol has been modified to reflect the results of the feasibility study. Official recruitment to the ICE cohort started in September 2015. The first patient was recruited on 2 October 2015.

## Abbreviations

AMD: Age-related macular degeneration
ANOVA: Analysis of variance
CarGOQoL: CareGiver Oncology Quality of Life
CES-D: Center for Epidemiologic Studies-Depression Scale questionnaire
CRA: Clinical Research Assistant
EQ-5D: European Quality of life – 5 dimensions questionnaire
HADS: Hospital Anxiety and Depression Scale
HRQoL: Health-related quality of life
ICER: Incremental Cost-Effectiveness Ratio
LASA: Linear Analogue Scale Assessment quality of life questionnaire
MCID: Minimal Clinically Important Ddifference
MMSE: Mini Mental State Examination
MOS SF-36: Medical Outcome Study Short Form-36 items
NYHA: New York Heart Association
QALY: Quality-adjusted life year
RSQ: Relationship Scales Questionnaire
SD: Standard deviation
SF-6D: Short Form – 6 dimensions
SSQ6: Six-item Short Form of the Social Support Questionnaire
TAS: Toronto Alexithymia Scale
VAS: Visual Analogue Scale
